### Evaluation of treatment response and remission

One of our secondary outcomes is treatment response (50% reduction in HDRS-17 score) and remission (≤7 on HDRS-17) at 8 weeks, and 4 and 6 months. For a subgroup of patients, this data will also be available for 9 and 12 months, as part of the extended follow-up. For each treatment condition, the percentage of participants that responds or is in remission will be calculated, for each time point. Kaplan Meier survival estimates will be calculated based on outcome after the eight-week treatment period and during follow-up. Scores will be compared using Cox regression analysis to take into account both the rate of response or remission and the time needed to reach response or remission.

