## Methods

### Study design

In this pragmatic randomized controlled trial (RCT), patients are randomly assigned to one of two treatment conditions. In the first condition, treatment consists of rTMS combined with CBT and continued antidepressant medication, which will hereafter be referred to as the rTMS arm. In the second condition, treatment consists of a switch from the current antidepressant medication to a tricyclic antidepressant (TCA) or augmentation with lithium or a second-generation antipsychotic, also in combination with CBT. This will be referred to as the medication arm. The trial consists of 8 weeks of unblinded treatment followed by a follow-up of the cohort at four and 6 months from baseline onward. For a subgroup of the patients, an extended follow-up will take place at nine and 12 months from baseline onward to assess effect decay or preservation. See Fig. 1 for the CONSORT flowchart. Patients in the medication arm who did not recover to the medication intervention can receive rTMS after completion of the first 8 weeks of treatment.

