### Sample size calculation

The sample size calculation is based on the outcome of the rTMS arm in comparison to the medication arm. To flag up a clinically significant difference between rTMS and medication, we took an effect size of d = 0.33, which corresponds to the lower boundary of a medium clinically meaningful effect [31] and is similar to effect sizes for research on antidepressant medication [32]. Alpha will be set at 0.05, with a power (1-beta) of 0.80. We will employ a two-sided repeated measures ANCOVA, with a total of six repeated measurements (baseline and measurements corresponding to rTMS treatment 5, 10, 15, 20, and 25). See also Table 1 for an overview and timepoints of the measurements. Based on HDRS-17 data from one of our previous studies, we expect the correlation between baseline and follow-up to be *r* = 0.59, and the correlation between follow-up measurements to be *r* = 0.69. The sample size calculation was performed in STATA version 15.1 and resulted in an estimated required sample size of 59 participants per condition. Compensating for possibly 10% loss to follow-up, the total sample size at baseline will be increased to 132 participants.

**Table 1 Tab1:** Overview of rTMS sessions and measurements during the treatment period. For participants in the medication arm, measurements will be done on days corresponding to treatment day 5, 10, 15, 20, and 25 of rTMS treatment

	Week 1					Week 2					Week 3					Week 4				
Day	1	2	3	4	5	1	2	3	4	5	1	2	3	4	5	1	2	3	4	5
rTMS	x	x		x	x	x	x		x	x	x	x		x	x	x		x		x
HDRS						x						x								x
BDI-II						x						x								x
	Week 5					Week 6					Week 7					Week 8				
Day	1	2	3	4	5	1	2	3	4	5	1	2	3	4	5	1	2	3	4	5
rTMS	x		x		x	x		x		x		x		x			x		x	
HDRS								x											x	
BDI-II								x											x	

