### Primary objective - depressive symptoms

Section A, B and D of the Structured Clinical Interview for DSM 5 disorders (SCID-I; 2018) will be used at baseline and after six and 12 months to assess depressive episodes and possible relapses/recurrences at follow up and extended follow-up. During intake, the SCID will also be used to assess presence of bipolar disorder or psychotic features. The SCID takes about 20 min to complete.

The Hamilton Depression Rating Scale 17 item version is an observer rated scale used to assess the severity of depressive symptoms (HDRS-17) [38]. The HDRS-17 is assessed during screening, treatment, follow-up and extended follow-up. Completion takes approximately 15 min. During the eight-week treatment period, the HDRS-17 will be administered every five rTMS treatments, and on corresponding days for participants in the medication arm. See Fig. 2 for the schedule during treatment. Response is defined as a ≥ 50% reduction in score on the HDRS-17, whereas remission is defined as a score of < 8. Response and remission will be determined after 8 weeks of treatment and at the final follow-up assessment of the RCT at 6 months after baseline.

The Beck Depression Inventory will be used in order to measure individual differences in depressive symptoms (BDI-II) [39]. Participants will be asked to fill in the BDI-II once every five rTMS sessions or on corresponding days when they are in the medication arm. See Fig. 2 for the schedule during treatment. Participants have to indicate on 21 items in how far these items describe themselves on a scale ranging from 0 to 3 resulting in a sum score between 0 and 63. The total score can further be divided into four ranges, describing the severity of depressive symptoms from minimal (0–13), mild (14-19), moderate (20-28) to serious depressive symptoms (29–63). Completion takes about 5 min.

Two questionnaires will be used to assess and quantify the level of treatment resistance. The Dutch Measure for quantification of Treatment Resistance in Depression (DM-TRD) quantifies treatment-resistant depression by assessing treatments in the depressive episode as well as functional impairment, comorbid anxiety, personality disorders and psychosocial stressors [40]. The DM-TRD generally takes 10-20 min to complete after the diagnostic interview. The Antidepressant Treatment History Form (ATHF) can be administered in 10 min or less, depending on the number of antidepressant trials of a patient [41].

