### Change in depression severity

Our primary outcome during the intervention is overall change in HDRS-17 depressive symptom severity during 8 weeks of treatment by condition (rTMS versus medication). Data will be collected at 6 timepoints: at baseline, and after 5, 10, 15, 20, and 25 rTMS treatment sessions (or corresponding days for participants in the medication arm). We will employ linear mixed modelling using marginal means, with HDRS-17 score as our dependent variable and treatment (rTMS or medication) as independent variable. Age and gender will be added as covariates, since these have been shown to affect the phenomenology of depression.

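### After week 8 the article states only cut-off analyses of the HDRS-17, which fit the 6-month improvement and 12-month decay aims poorly and use less of the information collected

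*Protocol article*

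**What the plan says.** The only full-scale model of the HDRS-17 is the linear mixed model under Change in depression severity: "Our primary outcome during the intervention is overall change in HDRS-17 depressive symptom severity during 8 weeks of treatment by condition". Its six timepoints run from baseline to the visit after session 25, at week 8.

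Collection does not stop there. Under Primary objective - depressive symptoms: "The HDRS-17 is assessed during screening, treatment, follow-up and extended follow-up".

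For 8 weeks, 4 and 6 months, and for 9 and 12 months in the extended subgroup of 92, the section Evaluation of treatment response and remission defines two binary outcomes (at least a halving of the score, and a score of 7 or less) and states: "For each treatment condition, the percentage of participants that responds or is in remission will be calculated, for each time point". It adds Kaplan-Meier estimates and compares the arms by Cox regression on the time taken to reach response or remission. The Effects section uses remission at 6 months for the cost-effectiveness analysis.

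The end of the Background sets the aims of testing clinical improvement and prevention of recurrence over 6 months. Study design says that "an extended follow-up will take place at nine and 12 months from baseline onward to assess effect decay or preservation".

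**The concern.** Decay or persistence concerns how the difference between arms changes between week 8 and later visits. The stated follow-up analysis answers a different question. A patient who remits at week 8 and relapses by month 6 still counts as an early success in a time-to-first-remission analysis. The percentages per visit could show such a loss, but only coarsely: scores of 8 and 30 are the same non-remission, while 7 and 8 differ.

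The risk is one of reading. In the smaller 12-month cohort, a cut-off comparison could easily be non-significant even if the whole planned effect were still present, and that result could be taken as loss of the rTMS effect. The Discussion counts information on durability among the trial's strengths, so readers will look for this answer.

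**Working it through.** **Inputs from Sample size calculation.** "we took an effect size of d = 0.33"; 5% significance and 80% power; "We will employ a two-sided repeated measures ANCOVA, with a total of six repeated measurements"; for the correlation with baseline, "we expect the correlation between baseline and follow-up to be *r* = 0.59"; correlation 0.69 between follow-up measurements; 59 per condition; 132 in total after 10% loss. Participants gives 92 for the extended follow-up, which is 46 per arm if split equally.

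**Reproducing the plan's figure.** With five post-baseline measurements the variance factor is (1 + 4 × 0.69)/5 − 0.59² = 0.752 − 0.3481 = 0.4039. Then n = 2 × (1.960 + 0.842)² × 0.4039 / 0.33² = 58.2, so 59 per arm. 118/0.9 = 131.1, so 132. Both stated figures reproduce.

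**Assumptions for follow-up.** The article gives neither a follow-up effect nor remission rates. I assume that d = 0.33 and r = 0.59 carry over to the later visits and that scores are normal. Medication-arm remission p0 is varied from 13% to 56%, the span of remission figures in the Background.

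**Full score, one visit.** Power = Φ(0.33/SE − 1.96), with SE = √(2/n) unadjusted and √(2 × (1 − 0.59²)/n) = √(2 × 0.6519/n) adjusted for baseline. For n = 59 the SEs are 0.184 and 0.149; for n = 46 they are 0.209 and 0.168.

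**Remission, one visit.** The same shift cut at a threshold gives p1 = Φ(Φ⁻¹(p0) + 0.33). Power is that of a two-sided two-proportion test with pooled null variance. Example: p0 = 0.13 gives p1 = 0.213; at n = 59 the null SE is 0.0694 and the alternative SE 0.0690, so power = Φ((0.083 − 1.96 × 0.0694)/0.0690) = 22%.

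| Analysis | 6 months, 59 per arm | 12 months, 46 per arm |
|---|---|---|
| Remission, 13% v 21.3% | 22.1% | 18.1% |
| Remission, 20% v 30.4% | 25.5% | 20.8% |
| Remission, 35% v 47.8% | 29.0% | 23.6% |
| Remission, 45% v 58.1% | 29.4% | 23.9% |
| Remission, 56% v 68.5% | 28.5% | 23.2% |
| Full score, unadjusted | 43% | 35% |
| Full score, baseline-adjusted | 60% | 50% |

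The 46 per arm allows for no loss. With 41 (10% lost) the 12-month figures are about 17-22%, 32% and 46%.

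**Share of power kept by remission.** On scale alone: 22.1/43.3 = 0.51 to 29.4/43.3 = 0.68 at 6 months, and 18.1/35.3 = 0.51 to 23.9/35.3 = 0.68 at 12 months. Against the baseline-adjusted score: 0.37-0.49 and 0.36-0.48.

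**Response.** Its definition already uses baseline, so the adjusted score is the fair comparator. Simulation with the plan's correlations (assumed baseline mean 22 and SD 4.5, follow-up SD 7, control mean 10-14) gives 35-40% against about 60% at 6 months, and 28-32% against about 49% at 12 months. Response keeps about 60-65%.

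**Time to first remission.** In the same simulations the log-rank test (the score test of the Cox model) has about 34-35% power over week 8, 4 and 6 months with 59 per arm, and 29-31% over five visits with 46 per arm. It pools several visits, so it is not like-for-like with a single-visit comparison.

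**The case against.** The strongest reply is that the article is condensed. It introduces response and remission as one of its secondary outcomes, not as the full list, and its Analysis section describes no model for the BDI-II, the symptom questionnaires or SCID recurrence either. A follow-up mixed model may stand in a fuller document. That limits the point: a reader might infer that the trial will never analyse the full score after week 8, and the article does not say so. What remains is that the article is not silent about these visits. It fixes a method for them, and that method does not measure change in the treatment difference.

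Second, response and remission match declared objectives. The aim covers recurrence as well as improvement, the SCID is repeated at 6 and 12 months, and the cost-effectiveness analysis uses remission. This stands, and is why those outcomes should stay. None of them estimates the size of the HDRS-17 difference over time. The QALY analysis uses follow-up data on a full scale, but of a different measure.

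Third, it is tempting to say that the cut-off halves the power. That mixes two effects: under half applies only when the gain from baseline adjustment is credited to the full score. It also concerns remission, not response, and a two-proportion test, whereas the named comparison is Cox regression, which could itself take baseline severity as a covariate. Against Cox over several visits, the unadjusted single-visit score gains less (43% against about 34-35% at 6 months; 35% against 29-31% at 12 months).

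Fourth, d = 0.33 belongs to the 8-week analysis. Study design lets medication-arm patients who have not recovered receive rTMS after week 8, and booster sessions are allowed for responders to rTMS who relapse, so full persistence is doubtful. This stands for all the absolute power figures; a smaller true difference lowers power on both scales.

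**Conclusion.** The concern holds for secondary aims. The follow-up analysis that the article states is a weaker use of scores already collected, and its time-to-event part cannot show loss of effect after a first response or remission.

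The size is moderate. Remission keeps roughly half to two-thirds of the single-visit power on scale alone, and under half once baseline adjustment is included. Response keeps about 60-65% of the baseline-adjusted power. These ratios rest on normal scores, the plan's 8-week effect and correlations persisting, and an assumed range of control remission rates.

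Two stronger inferences are not supported. The primary 8-week comparison is analysed on the full scale and is untouched. And no power is claimed here for the change in treatment difference from week 8: every figure above concerns a difference at one visit or a time to event, so the calculation does not show that the decay question would be well powered on the full scale either. The case for that contrast is that it addresses the stated question.

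**What to change.** In Change in depression severity and Evaluation of treatment response and remission, add one secondary analysis:

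- a linear mixed model of the HDRS-17 with week 8, 4 and 6 months (and 9 and 12 months in the extended subset) as categorical visits, treatment-by-visit terms, and baseline HDRS-17 as covariate;
- the rTMS-minus-medication mean difference with 95% CI at each visit;
- the change in that difference from week 8 to each later visit, named as the measure of decay or preservation;
- a sentence saying that after week 8 the contrast compares treatment strategies as the protocol allows them, including rTMS in the medication arm.

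Keep the response and remission analyses as supporting secondary outcomes, and remission for the cost per remitter. The change is to wording only, with no further patients, visits or assessments. The cost is one more secondary analysis to report and to place among the secondary outcomes.

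### Cox regression from week 8 onward cannot show the speed of response or remission during treatment, and no between-arm comparison of current status is named

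*Protocol article*

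**What the plan says.** All references are to the protocol article.

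- **Evaluation of treatment response and remission.** Response and remission on the HDRS-17 are secondary outcomes at 8 weeks, 4 months and 6 months, and also at 9 and 12 months in a subgroup. Percentages per arm are given visit by visit. The basis of the survival curves is stated as follows: "Kaplan Meier survival estimates will be calculated based on outcome after the eight-week treatment period and during follow-up". On how the arms are then compared, the section says: "Scores will be compared using Cox regression analysis to take into account both the rate of response or remission and the time needed". No other comparison between the arms is named there.
- **Primary objective - depressive symptoms.** Response and remission are determined at 8 weeks and 6 months only. The SCID is repeated at 6 and 12 months "to assess depressive episodes and possible relapses/recurrences at follow up and extended follow-up".
- **Change in depression severity; Table 1.** HDRS-17 is scored at treatment sessions 5, 10, 15, 20 and 25, or on corresponding days in the medication arm. Table 1 puts these in weeks 2, 3, 4, 6 and 8.
- **Study design.** Medication patients who did not recover may receive rTMS after the first 8 weeks.
- **Background; Interventions, rTMS.** Prevention of recurrence over 6 months is an aim, and relapse after response to rTMS is foreseen.

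**The concern.** The Cox model is chosen to capture how long patients take to reach response or remission. The data it is given start when the randomised treatment period ends. A patient who first remits in week 3 or 4 is dated to week 8 at the earliest, exactly like one who first remits in week 8. The rTMS section itself uses in-treatment scores to identify remission: treatment may end from session 15 after two successive scores below 8, which means remission by session 10 at the latest (week 3). That information does not reach the time-to-event analysis.

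Two further problems concern what the hazard ratio would mean:

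- A first-event model treats remission as permanent, although the plan expects relapse and gives no rule for lost remission.
- The medication patients still at risk of a first remission after week 8 are largely those who may now receive rTMS, so the later part of the hazard ratio does not cleanly compare rTMS with medication.

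At stake is the reading of a secondary outcome. A real difference in speed could go unseen, and an early gain that is later lost could be reported as an advantage.

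**Working it through.** **1. The plan's own figure.** The only sizing is for the primary comparison. Its inputs are the error rates, "Alpha will be set at 0.05, with a power (1-beta) of 0.80"; the size of effect, "we took an effect size of d = 0.33"; the model, "We will employ a two-sided repeated measures ANCOVA, with a total of six repeated measurements" (one baseline, five later); the correlation among later scores, "and the correlation between follow-up measurements to be *r* = 0.69"; and the correlation of these with baseline, "we expect the correlation between baseline and follow-up to be *r* = 0.59".

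n per arm = 2 × ((1.960 + 0.842)/0.33)² × [(1 + 4 × 0.69)/5 − 0.59²] = 144.1 × (0.752 − 0.348) = 144.1 × 0.404 = 58.2, rounded up to 59. Then 118/0.9 = 131.1, giving 132. The stated size reproduces. No figure is given for the Cox analysis.

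**2. Which visits can carry an event.** Week 8, 4 and 6 months for everyone; also 9 and 12 months for 92 patients, leaving 132 − 92 = 40 with three visits. The session-25 score is the week-8 outcome, so four of the five in-treatment scores (weeks 2, 3, 4 and 6) are not used.

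**3. Concentration of events.** The Background cites remission of 56% for rTMS with CBT and 13% for a later medication trial. These are not design assumptions. With 66 per arm, 66 × 0.56 = 37.0 and 66 × 0.13 = 8.6, so about 46 of 132 patients would share the single event time of week 8.

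**4. Simulation of the planned analysis.** 400 trials per scenario, 66 per arm, remission defined as HDRS-17 below 8, correlation 0.69 between all visits, Efron ties. Assumed and not in the document: SD 6.5, the mean trajectories, a random choice of the 92 patients, no dropout and no crossover. A hazard ratio above 1 favours rTMS.

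| Scenario | In remission at week 8, rTMS v medication | At 6 months | Cox from week 8: HR (rejection) | Cox on all visits: HR (rejection) |
|---|---|---|---|---|
| No difference | 32% v 32% | 32% v 32% | 1.01 (5.8%) | 1.00 (5.0%) |
| A: rTMS faster in treatment, equal from week 8 | 32% v 33% | 32% v 33% | 0.98 (4%) | 1.27 (17%) |
| B: rTMS better at week 8, then relapse | 50% v 32% | 22% v 32% | 1.23 (15%) | 1.29 (19%) |

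In A, the planned model shows nothing of the speed difference; the in-treatment scores reveal it. In B, the difference in status goes from 50 − 32 = +18 points at week 8 to 22 − 32 = −10 points at 6 months, yet the hazard ratio favours rTMS with either set of visits. Only status by visit shows the reversal. Of patients in remission at some visit from week 8 to 6 months, 36% (no difference, A) to 50% (B) are not in remission at 6 months. The share of first remissions that fall on week 8 is 57% to 72%.

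**5. Ties.** A separate simulation (600 trials per scenario, exponential times grouped to 8, 17.3 and 26 weeks, assumed control remission by week 8) gave HR and power:

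| True HR, control remission | Breslow | Efron | Complementary log-log |
|---|---|---|---|
| 2, 25% | 1.75, 82% | 2.00, 91% | 2.04, 92% |
| 2, 35% | 1.66, 83% | 1.98, 95% | 2.06, 96% |
| 1.5, 35% | 1.34, 31% | 1.48, 51% | 1.50, 52% |

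With no difference, Breslow rejected 1.7%, so it is conservative. Efron is within one percentage point of power of the grouped-time model.

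**The case against.** The strongest reply is that the plan as a whole does follow current status. Percentages per arm are reported at each visit, the cost-effectiveness analysis uses remission at 6 months as its central clinical outcome and relates cost to remitters, and the SCID records relapse. A reader might infer that relapse is ignored; the document does not support that. What stands is narrower: the response and remission section names no between-arm comparison of status, and the one it does name cannot see lost remission.

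A reader might also infer that heavy ties make the Cox result badly biased or invalid. That does not follow. The attenuation arises under Breslow and nearly disappears under Efron. The article chooses no tie method, which is a detail for the analysis plan. Nor is it right that only three visits exist: 92 of 132 patients have five.

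The wording about the survival estimates is loose, and the full analysis plan, which is not shown, could bring in the earlier scores. That is fair, but the article names the visits and the source of the estimates, and on its plain wording the earlier scores are outside.

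Finally, counting late remissions in the assigned arm is consistent with intention to treat in a pragmatic trial, and comparing status at 4 and 6 months does not remove the crossover. Both points stand. Crossover limits how the later results can be read; it is not an argument that status comparisons would cure it.

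**Conclusion.** The point holds for the stated between-arm analysis of response and remission and should be corrected; it does not reach the primary analysis or the sample size. The method does not serve its stated purpose during the randomised treatment period, and past week 8 it treats a reversible state as permanent. That conclusion rests on the wording of the article and needs no simulation.

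The sizes are illustrations. A hazard ratio of 0.98 instead of 1.27 for a pure speed advantage, and 1.23 in favour of an arm that is about 10 points worse at 6 months, depend on assumed trajectories and SD. Even with all visits, scenario A was detected in only 17% of trials: the added scores make speed visible without giving good power. The all-visits model in the check also included follow-up visits, so it is not exactly the analysis proposed below. Crossover was not simulated, so no size is claimed for it. Ties are a minor matter.

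**What to change.** 1. Make the comparison of current response and remission status between arms the secondary analysis, at week 8 (main) and at 4 and 6 months, with a repeated binary model adjusted for baseline HDRS-17 and the stratification factors.
2. Confine time to first response or remission to the 8-week treatment period. Use all five in-treatment HDRS-17 scores in a discrete-time (complementary log-log) model, or Cox with Efron ties.
3. For durability, report remission at week 8 that is maintained at 4 and 6 months, with rTMS use in the medication arm shown, and state that these later comparisons remain affected by crossover.
4. Reconcile the depressive-symptoms measures section (8 weeks and 6 months) with the response and remission section (8 weeks, 4 and 6 months) on the visits at which the outcomes are determined.

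The cost is revised analysis wording and a little more analysis work with standard models. No new data are needed.
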